#### Community Engagement

The essence of the Acceset intervention draws on emerging adult support within the Singapore ecosystem and community by tapping into the shared experiences among emerging adults and training them to harness the 4 components of psychological well-being to bolster each other’s mental well-being (Figure 2). Seekers can further the community efforts by joining as befrienders and being trained to provide web-based peer support. By engaging clinicians, psychologists, and counselors, the Acceset intervention emphasizes the availability of peer support that leverages the lived experiences of the community. The building of the seeker-befriender-moderator relationship also aims to deepen the authenticity of peer support rather than being a “transaction” for referral, as evidenced by the effective implementation of the intervention when seekers’ and befrienders’ satisfaction with the support system and sense of perceived social support relate positively to their psychological well-being.

In addition to a community-based structure for facilitating digital peer support, Acceset engages education stakeholders at various IHLs in the advice of safety standards and protocols for effective and compliant digital peer support that is in accordance with the ethics of members of the helping profession. Education stakeholders play an important role in normalizing a new service delivery model through various formal and informal outreach channels. This could entail mass mailing of a new service and organization of an information session where students can learn more about the new service and how participating in it can be beneficial for their mental well-being. Attending college can be a particularly stressful time, especially in Asian societies with a high cultural value ascribed to educational achievement and a high level of competition [49,50]. The experience of heightened psychological distress is a salient problem, with an average of 20% to 40% of students reporting distressed symptoms [50]. This finding, coupled with the increasing number of emerging adults enrolled in 2- or 4-year colleges (40% in 2013 to 70% in 2018) [51], provides the impetus for leveraging a community approach in the development of digital peer support that intervenes in emerging adults’ psychological well-being.

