**Aims and hypotheses**
Aim 1: the first aim is to evaluate the implementation effectiveness of digital peer support training between emerging adults providing support (befrienders) and emerging adults seeking help (seekers).Research question 1a: is Acceset digital peer support training an effective training curriculum in providing peer support?Hypothesis 1a: the digital peer support training is effective for befrienders in providing peer support, as demonstrated by the adoption of and fidelity to the training curriculum.Research question 1b: is the Acceset text-based intervention (ie, the platform) feasible and acceptable (ie, safe and timely) as an ongoing mechanism of support for seekers and befrienders?Hypothesis 1b: digital peer support is feasible and acceptable in offering support for emerging adults’ mental well-being, which is evidenced by 2 indicators:The engagement of the seeker-befriender-moderator interaction across the 4 time points—baseline (before the intervention), 3 weeks (conclusion of the intervention), and 6 and 9 weeks (carryover effect assessment)—that is indexed by the waiting period for seekers to receive a response. Delays are defined as a >48-hour waiting period and will be categorized based on the following reasons: (1) technical factors (eg, the befriender is not able to log into the platform to respond in time) and (2) human factors (eg, the befriender drops out from the study, and no replacement is found in time). An acceptable response time is within 48 hours, and this is emphasized during Acceset digital peer support training for befrienders [37].The use of technical features of the Acceset platform that is measured by the seeker dropout rate at each stage of engagement with the Acceset platform, the number of visits on the study registration website, the number of participants who registered with Acceset, the average number of letters exchanged, and the average number of emotion and functional adjustment stickers and motivation graphic interface formats used [37].Research question 1c: is the Acceset text-based intervention (ie, the platform) feasible and acceptable (ie, safe and timely) as an ongoing mechanism of support that identifies individuals who are at an unacceptably high risk of mental health conditions?Hypothesis 1c: digital peer support is feasible and acceptable in offering support for emerging adults’ mental well-being by identifying individuals who are at an unacceptably high risk of mental health conditions related to depression and suicidality, which is measured before and during engagement based on 3 means—specifically, the Acceset algorithm detection of the content of the letters, the moderators’ vetting of the content of seekers’ letters, and the seekers’ self-report responses to the 9-item Patient Health Questionnaire [38] (refer to the Implementation Outcomes section for details [37]).Aim 2: the second aim is to elucidate whether Acceset digital peer support harnesses the 4 components of emerging adult mental health—mattering, selfhood, compassion, and mindfulness.Research question 2a: does Acceset digital peer support enhance the 4 components among seekers and befrienders?Hypothesis 2a: Acceset digital peer support (training) increases the 4 components among befrienders (before and after training) and seekers (over the course of the study across 4 time points).Research question 2b: is Acceset digital peer support effective in improving emerging adult mental well-being?Hypothesis 2b: digital peer support leads to significantly better mental well-being of seekers compared with the control group. This effect is sustained beyond the period of the intervention.Aim 3: the third aim is to investigate the mechanism of change in emerging adult mental well-being involving digital peer support (delivered by the Acceset platform).Research question 3: what is the mechanism explaining the change in emerging adult mental well-being involving digital peer support?Hypothesis 3: the initial level and rate of change (ie, growth factors) of befrienders’ web-based support positively predict the growth factors of seekers’ psychological well-being in accordance with latent growth curve modeling.

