#### Implementation Outcomes

For research question 1a and hypothesis 1a, we will determine whether Acceset digital peer support training is an effective curriculum for befrienders in providing effective peer support. We will assess the adoption of and fidelity to the training curriculum through the letter exchanges between seekers and befrienders. The text of the letter exchanges will be evaluated in terms of the extent to which befrienders display fidelity in applying the 4 components of psychological well-being in response to seekers’ disclosure. All correspondence will be anonymized before analysis, and the seekers’ letters will only be used to provide content for the befrienders’ responses. With respect to research question 1b, hypothesis 1b, research question 1c, and hypothesis 1c, we will evaluate the feasibility and acceptability of sustaining access to web-based peer support in terms of (1) initial and sustained engagement of seekers, befrienders, and moderators (ie, certified counselors); (2) the use of technical features of the Acceset platform; and (3) the identification of participants with high risk of mental health conditions relating to depression and suicidality.

This study will assess the waiting period for a seeker to receive a response. Delays (defined as a >48-hour waiting period) will be categorized based on the following reasons: (1) technical factors (eg, the befriender is not able to log into the platform to respond in time) and (2) human factors (eg, the befriender drops out from the study, and no replacement is found in time). An acceptable response time is within 48 hours, and this is emphasized during Acceset digital peer support training for befrienders. The seeker dropout rate at each stage of engagement with the Acceset platform will be assessed based on (1) the number of visits to the study registration website, (2) the number of participants who registered with Acceset, (3) the average number of letters exchanged, and (4) the average number of emotion and functional adjustment stickers and motivation GIFs used.

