#### Clinical Outcomes

To address research question 2a and hypothesis 2a, we will examine whether the Acceset training curriculum can enhance the 4 components of psychological well-being among befrienders and seekers. We will compare the change in mattering, selfhood, compassion, and mindfulness scores of befrienders between baseline and following Acceset training (ie, before vs after training) and those of seekers over the course of the study. As for research question 2b and hypothesis 2b, we hypothesized that engagement with Acceset digital peer support will lead to improved mental well-being of the seekers compared with the control group and that this effect may be sustained beyond the period of the intervention. To assess these effects, we will evaluate the change in mental well-being of the participants in both study groups (intervention and control) after 3, 6, and 9 weeks from baseline using self-report questionnaires. Seekers will provide responses pertaining to help-seeking behavior beyond the Acceset platform at weeks 6 and 9 using the perceived social support measure in the questionnaire battery. We will assess the correlations of the 3 digital features—comprising emotion and functional adjustment stickers and motivation GIFs, which reflect seekers’ mental well-being during engagement with the platform—with their well-being scores from the questionnaires.

The scale or set of scales used to assess the clinical outcomes, including the 4 components of psychological well-being underpinning the Acceset training curriculum, measures of seekers’ well-being, and perceived social support, are outlined in the following paragraph.

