“Mattering” will be assessed via the Rosenberg Mattering Scale [52]. *Selfhood* comprises self-knowledge, interpersonal self, and self-agency and will be assessed via the following respective scales: the Rosenberg Global Self-Esteem Scale [53], the Self-Consciousness Scale [54], and the General Self-Efficacy and Social Self-Efficacy Scales [55]. *Compassion* will be assessed as operationalized in the Compassion Cultivation Training [56] comprising three stages: (1) an awareness of distress, (2) affective concern, and (3) a responsiveness or readiness to help relieve that distress (motivational). *Mindfulness* will be regarded as a flexible cognitive state in which individuals are actively present and notice novel aspects in both the environment and one’s perspectives [45]. We will evaluate the participants’ responses based on the degree to which they harness the approaches pertaining to the enhancement of mindful self-acceptance: (1) identifying novel aspects of the situation or perspective; (2) demonstrating “work in progress” by using possibility words such as “could be” and offering other interpretations of the situation their peers have shared; (3) highlighting puzzles and paradoxes in the peer-disclosed emotional experiences (eg, how their peers may feel victimized yet are responsible for being in that situation), which builds tolerance for ambiguity and decreases the experience of psychological symptoms; (4) noticing humorous aspects of the situation; (5) perceiving the situation from multiple perspectives; (6) considering alternative (useful) aspects of a problematic context or the silver lining; (7) emphasizing a mental file of positive memories; and (8) encouraging peers in mindfulness journaling. *Anxiety* will be measured using the Generalized Anxiety Disorder Questionnaire [57]. *Depression* will be measured using the PHQ-9 [38]. *Perceived social support* will be assessed using the Multidimensional Scale of Perceived Social Support [58].

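### The Community Engagement section offers as evidence of effective implementation a correlation among users that requires no intervention effect and that the formal implementation outcomes do not use

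*Protocol article*

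**What the plan says.** The sentence is in the protocol article, Methods, Community Engagement, within the description of the intervention. It concerns the authenticity of the seeker-befriender-moderator relationship, and treats implementation as shown to be effective "when seekers’ and befrienders’ satisfaction with the support system and sense of perceived social support relate positively to their psychological well-being". It names no arm, time point, size or test.

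Perceived social support "will be assessed using the Multidimensional Scale of Perceived Social Support" (Clinical Outcomes). The same section uses that measure for help-seeking outside Acceset at weeks 6 and 9. Satisfaction appears otherwise only through the CSQ-8 in the legend of Figure 1, so Community Engagement is the one place in the article that says how satisfaction will be interpreted.

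The formal text defines implementation differently. Hypothesis 1a judges the training "as demonstrated by the adoption of and fidelity to the training curriculum". For hypotheses 1b and 1c, Implementation Outcomes says "we will evaluate the feasibility and acceptability of sustaining access to web-based peer support in terms of" engagement, use of technical features and identification of high-risk participants. Effectiveness is separate: hypothesis 2b states that "digital peer support leads to significantly better mental well-being of seekers compared with the control group", and Clinical Outcomes adds that "we will evaluate the change in mental well-being of the participants in both study groups (intervention and control) after 3, 6, and 9 weeks".

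**The concern.** Evidence of effective implementation should behave differently when the intervention works and when it does not. A correlation among users need not. People who feel well supported in life may report better well-being with or without Acceset, and the support scale is a general one that the article itself applies to support outside the platform. Contented people may also report more satisfaction with whatever they are given.

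At stake is a route to a success claim that bypasses both the control arm and the formal implementation outcomes. A background association could be reported as successful implementation.

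**Working it through.** **The plan's own figure.** The article gives none for this criterion. Its 50 per arm at alpha .05 and 80% power cannot be reproduced, because no effect size is stated. Solving backwards, d = (1.960 + 0.842) × √(2/50) = 0.56 (0.566 by the t test). That value is used below only as a realistic size of shift.

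**Step 1: does the criterion respond to an effect?** With scores oriented so that higher is better, r = Σ(x − x̄)(y − ȳ) / √[Σ(x − x̄)² Σ(y − ȳ)²]. If every user's well-being y moves by a constant c, ȳ moves by c too. Every deviation, and so r, is unchanged. A numerical check with shifts of +0.57, 0 and −0.57 SD gave the identical r. The same algebra covers uniformly low satisfaction (shift x instead) and correlations of change scores. An effect that varies between users could alter r, but a positive r does not show that it did.

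**Step 2: how often could it be met with no Acceset effect?** Inputs from Participants and Study Setting: 50 seekers and 30 befrienders using Acceset. The two-sided .05 level is the article's general setting, not one attached to this sentence. The background correlation ρ is an assumption, ranged from 0 to 0.5. Participants are treated as independent and normally distributed.

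For one correlation, by Fisher's z with SE = 1/√(n − 3):
- P(r > 0) = Φ(atanh ρ / SE)
- P(significant and positive) = 1 − Φ(1.96 − atanh ρ / SE)

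Example with n = 50 and ρ = 0.3: atanh 0.3 = 0.310, SE = 1/√47 = 0.146, ratio 2.12. P(r > 0) = Φ(2.12) = 98%. P(significant) = 1 − Φ(1.96 − 2.12) = 56%.

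The sentence joins two measures and two groups, so its full reading is four correlations. These were simulated 20,000 times for each ρ. The columns for all four use the same ρ among all three variables. The last column makes satisfaction unrelated to the other two.

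| ρ | One, n=50: positive | One, n=50: significant | All four positive | All four significant | All four positive, satisfaction unrelated |
|---|---|---|---|---|---|
| 0 | 50% | 2.5% | 6% | <0.1% | 6% |
| 0.1 | 75% | 10% | 30% | <0.1% | 13% |
| 0.2 | 92% | 28% | 64% | 0.4% | 20% |
| 0.3 | 98% | 56% | 88% | 6% | 23% |
| 0.4 | >99% | 83% | 97% | 31% | 24% |
| 0.5 | >99% | 96.5% | >99% | 67% | 25% |

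The ceiling in the last column follows directly: with no relation, satisfaction has a positive sign half the time in each group, and 0.5 × 0.5 = 25%.

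**Step 3: does it match the formal outcomes?** Aims and hypotheses and Implementation Outcomes use adoption and fidelity coded from letters, response within 48 hours, dropout, feature use, and identification and referral of high-risk seekers. None is a correlation of satisfaction or support with well-being.

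**The case against.** The strongest reply is that this is descriptive prose and not a decision rule. The outcomes section undertakes to list the measures for each hypothesis, and this correlation is not among them. It is also absent from the analysis text and from the hypotheses restated in the Discussion. The intervention effect has its own controlled hypothesis and between-group t tests, which the correlation cannot override. All of this stands. A reader might infer that the trial's implementation verdict rests on the correlation, and the documents do not support that.

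A reader might also infer that the criterion would usually be met if Acceset did nothing. That requires reading a positive relation as sign only and assuming a positive background correlation for both measures. On the strict reading, with all four significant, it passes half only near ρ = 0.5.

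Nor can it be said that the wait-list arm would show the same associations throughout. Wait-listed seekers have not used Acceset during the comparison, so they have no satisfaction with it to correlate. Only the perceived-support half can be compared between arms.

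Finally, the time point and metric of the correlation may be fixed in a fuller document, so their absence is not held against the article. Step 1 applies whatever time point or metric is chosen.

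**Conclusion.** The point holds, as a minor one. That the criterion neither requires nor measures an intervention effect needs no assumption, and neither does its mismatch with the formal implementation outcomes.

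How often it would be met without an effect does rest on assumptions. For ρ from 0.2 to 0.5 on both measures, the range is about 64% to over 99% on the sign reading and about 0.4% to 67% if all four must be significant. It is at most about 25% on the sign reading if satisfaction is unrelated to well-being. These figures use the planned 30 befrienders; Results reports 35 recruited. The supportable statement is that the criterion could be met without any effect, not that it usually would be. No planned test or sample size depends on the sentence.

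**What to change.** In Community Engagement, remove the correlation as evidence of effective implementation, label it descriptive, and refer to the outcomes in Aims and hypotheses and Implementation Outcomes.

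Rest any claim that Acceset raised perceived support on the arm 1 versus arm 2 difference in the Multidimensional Scale of Perceived Social Support at week 3, adjusted for baseline, with its 95% CI. The baseline adjustment improves on the planned unadjusted t test. This covers seekers only, since befrienders have no randomised comparison group. It assumes that arm 2 completed the scale at baseline and week 3, which the planned between-arm comparison of the battery implies but does not state outright.

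Report the arm 1 mean CSQ-8 with its 95% CI as a description of satisfaction. Without a threshold it is not a success criterion.

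Results says data collection ended in June 2022 and analysis began in July 2022, so disclose that the change was made after data collection.

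The cost is a wording change and one adjusted comparison on data that should already be in hand. The downside is that a claim of effective implementation becomes harder to make.

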**Figure 2 figure2:**
[figure not shown]
The Acceset intervention draws on digital peer support within the Singapore ecosystem and community.

### Implementation and Clinical Study Outcomes

All implementation and clinical outcomes will be measured via the engagement with Acceset over 4 time points using the aforementioned questionnaire battery [37]. In this section, we delineate the outcome measures that correspond to each hypothesis examined in this study.

#### Implementation Outcomes

For research question 1a and hypothesis 1a, we will determine whether Acceset digital peer support training is an effective curriculum for befrienders in providing effective peer support. We will assess the adoption of and fidelity to the training curriculum through the letter exchanges between seekers and befrienders. The text of the letter exchanges will be evaluated in terms of the extent to which befrienders display fidelity in applying the 4 components of psychological well-being in response to seekers’ disclosure. All correspondence will be anonymized before analysis, and the seekers’ letters will only be used to provide content for the befrienders’ responses. With respect to research question 1b, hypothesis 1b, research question 1c, and hypothesis 1c, we will evaluate the feasibility and acceptability of sustaining access to web-based peer support in terms of (1) initial and sustained engagement of seekers, befrienders, and moderators (ie, certified counselors); (2) the use of technical features of the Acceset platform; and (3) the identification of participants with high risk of mental health conditions relating to depression and suicidality.

This study will assess the waiting period for a seeker to receive a response. Delays (defined as a >48-hour waiting period) will be categorized based on the following reasons: (1) technical factors (eg, the befriender is not able to log into the platform to respond in time) and (2) human factors (eg, the befriender drops out from the study, and no replacement is found in time). An acceptable response time is within 48 hours, and this is emphasized during Acceset digital peer support training for befrienders. The seeker dropout rate at each stage of engagement with the Acceset platform will be assessed based on (1) the number of visits to the study registration website, (2) the number of participants who registered with Acceset, (3) the average number of letters exchanged, and (4) the average number of emotion and functional adjustment stickers and motivation GIFs used.

With regard to user referral to appropriate mental health support providers, the seeker-befriender-moderator interaction will identify participants at an unacceptably high risk of depression and suicidality before and during engagement based on 3 means. First, the Acceset algorithm will scan the content of the letter exchanges for high negativity and suicidal thoughts and expressions. Second, moderators with the required background and assessment tools will identify seekers at risk by vetting all the letter exchanges for high negativity and suicidal thoughts and expressions. Third, seekers will self-report their responses to the PHQ-9, and those that meet the clinical cutoff scores (PHQ-9 >9) will be excluded at the start of the study. During the course of the study across the 4 time points, seekers with an unacceptably high risk of depression and suicidality (PHQ-9 >9) will be referred to an appropriate mental health care provider, including counseling centers and hotlines, on the NUS campus. Seekers’ self-reported responses to the PHQ-9 serve as the primary risk assessment to make referrals to appropriate mental health support providers.

At recruitment, we will assess the percentage of participants identified as being at an unacceptably high risk of depression and suicidality meeting the clinical cutoff of PHQ-9 >9 that has a sensitivity of 88% and specificity of 88% for major depression [38] and exclude them from the study. During the course of the study, we will ascertain the percentage of events when a befriender correctly alerts the moderator that the seeker is at an unacceptably high risk of depression and suicidality as confirmed by the moderator, who will vet every letter exchange. During the course of the study and for every letter exchange, we will tabulate the percentage of events when a moderator correctly identifies a seeker with an unacceptably high risk of depression and suicidality. Both the befrienders and moderators will use the PHQ-9 as a systematized coding structure to code seekers’ letter content to ensure generalizability and validity in risk assessment across both coders—befrienders and moderators. Finally, we will tabulate the percentage of events when a seeker who is at an unacceptably high risk of depression and suicidality (both during the recruitment process and during engagement with the platform) receives directions to an appropriate mental health care provider, including counseling centers and hotlines, on the NUS campus.

The study team will alert the counseling center on the NUS campus about the referrals of at-risk seekers to ensure that adequate and appropriate support is provided to them. In addition, at weeks 6 and 9, there will be a follow-up on all seekers (to measure carryover effects), which helps ensure the psychological safety of the seekers. At the start of the study, all seekers are provided with the participant informed consent and information sheet, which states that they will be referred to and their information shared with the NUS counseling center if their risk assessment across the 4 time points indicates an unacceptably high risk of depression and suicidality (PHQ-9 >9).

